## Method

The HOPES feasibility trail began enrolment in February 2023 and expects to complete data collection in mid-2024.

The HOPES study utilizes a convergent parallel mixed-methods, single-arm repeated measures trial design aiming to assess the feasibility of Swedish massage as an adjunct approach to care for pregnant women who have previously experienced stillbirth. The convergent parallel mixed-methods design collects and analyses quantitative and qualitative individually, then compares and relates the two data types for areas of convergence or divergence and then interprets the meaning of the combined results. The primary quantitative outcomes are the feasibility and acceptability of the massage intervention. Secondary outcomes include determining the optimal timing of massage treatments and the collection of measures for anxiety, worry, stress and self-management. A thematic analysis of women’s experiences from a subsample of participants undertaking the intervention will also be conducted. The study intervention consists of up to five 60-min pregnancy massage treatments over a 4-month period at individualized time intervals per participant’s choice or availability. Each participant will complete outcome measures pre- and post-study intervention. Participants will complete a short outcome measure each pre- and post-massage treatment. A narrative and joint display approach to integrate mixed-methods data is planned.

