### Criteria for discontinuing the intervention

The intervention will cease if participants are advised by their obstetric healthcare providers (i.e. on bed rest), if they are no longer pregnant or if the study participant delivers their baby prior to completing the allocated study intervention.

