#### Validated self-reported questionnaires

Worry, anxiety, coping, self-efficacy, stress and empathy will be assessed in the study via the following questionnaires:oWorry will be assessed via the *Cambridge Worry Score* (48) which is 17-item instrument that measures the content and extent of worries in pregnancy (48, 49). The total score range is from ‘zero to 85 with a higher score representing greater severity of worries’ (48).oMaternal anxiety symptoms will be assessed *using the Generalized Anxiety Disorder Assessment (GAD-7)* (50) which is a 7-item instrument that measures the severity of generalised anxiety disorder. The total score range is from zero to 21 with scores of 5–9 representing mild anxiety, 10–14 moderate anxiety and 15–21 representing severe anxiety (50)*.*oCoping via* the self-reported Revised Prenatal Coping Inventory (NuPCI)* (51) will be assessed. This scale has 32 items that evaluate the coping strategies of pregnant (51). The NuPCI consists of 3 subscales: positive attitude (15 items), avoidance (11 items) and spiritual-positive coping (6 items) (51). A higher score indicates more frequent use of a specific coping strategy (51).oSelf-efficacy via the *Strategies Used by People to Promote Health measure (SUPPH-29)* (52) will be assessed. This scale has 29 items that measure self-care self-efficacy (52). The SUPPH-29 consists of 3 sub-scales positive attitude (16 items), stress reduction (10 items) and decision making (3 items) (52). The total score range is from 29 to 145 with a higher score indicating greater self-confidence to carry out self-care strategies (52).oMaternal stress symptoms via the *Perceived Stress Scale* (PSS) (53) will be assessed. The scale has 10 items that measure perceived personal stress (53). The total score range is from zero to 40 with a score ranging from 0 to 13 considered low stress, 14–26 moderate stress and 27–40 high stress (53).oEmpathy in the context of the therapeutic relationship via the *Consultation and Relational Empathy (CARE) patient-reported experience measure (PREM)* (54). This scale has 10 items that measures patients’ perceptions of relational empathy in the consultation (54). The total score range is from 10 to 40 with higher scores indicating greater perceived relational empathy (54).o*Measure Yourself Concerns and Wellbeing (MYCaW)* assesses patient-reported outcomes *(PROM)* (46). This measure has the space for participants to write down two concerns they want help with, and then, the concerns are rated for severity using a 6-point Likert scale ranging from ‘not bothering me at all (0)’ to ‘bothers me greatly (6)’. A person’s wellbeing is also rated using the same 6-point Likert scale. There are two open-ended questions that ask if anything else important is happening in the person’s life and what has been most important about the treatment they received.

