#### Data collection

Some women may give birth before receiving their allocated treatments. Intervention delivery and data collection will cease for participants who give birth prior to completing the full study protocol, and collected data will be kept within the data set. Attempts will be made to collect the final quantitative and qualitative data from participants who fall into this category. The inclusion criteria for participants to be no more than 30 weeks of gestation (Table 1) are in place to minimise participants giving birth prior to completing the full study protocol. Participants who give birth prior to completing the full study protocol will be emailed inviting them to complete the post-intervention online questionnaires and informing them that they are able to participate in the in-depth interview (if applicable) if they desire. A follow-up email will be sent 2 weeks after the first email.

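### The e-mail rule for women who give birth before completing the protocol has no condition on the outcome of the birth, so read literally it also invites a woman with a new stillbirth to complete pregnancy-specific scales

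*Protocol article*

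**What the plan says.** The Data collection section of the protocol article deals with women who give birth before finishing the study. It first states that "Intervention delivery and data collection will cease for participants who give birth prior to completing the full study protocol". It then says: "Attempts will be made to collect the final quantitative and qualitative data from participants who fall into this category". The contact rule follows: "Participants who give birth prior to completing the full study protocol will be emailed inviting them to complete the post-intervention online questionnaires". The same message tells women that the interview remains open to them, where it applies, if they want it. Finally, "A follow-up email will be sent 2 weeks after the first email". No sentence in the section refers to the outcome of the birth.

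The criteria for discontinuing the intervention do draw a distinction. Besides obstetric advice, massage stops "if they are no longer pregnant or if the study participant delivers their baby prior to completing the allocated study intervention". That section governs the massage only, not later contact.

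On what is collected at the end, the Method section says "Each participant will complete outcome measures pre- and post-study intervention". Table 2 marks the Cambridge Worry Score at enrolment and after the intervention. The article describes that score as a "17-item instrument that measures the content and extent of worries in pregnancy". Of the Revised Prenatal Coping Inventory it says: "This scale has 32 items that evaluate the coping strategies of pregnant" (the sentence breaks off there). The post-intervention questionnaire also contains item Q.M, on feeling supported, which feeds one of the progression criteria.

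**The concern.** Every participant has had a stillbirth or a termination for medical reasons from 20 weeks, so a further loss is the foreseeable exceptional case in this trial. If the rule is followed as printed, a woman whose baby has died again would receive an invitation to rate her worries in pregnancy and her prenatal coping, and then a follow-up. The Background itself warns that care in this population can worsen stress and revive traumatic memories.

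There is also a measurement issue, and it is wider than bereavement. A pregnancy-worry or prenatal-coping score given once the pregnancy is over does not measure what it measured at enrolment. The analysis section nevertheless compares baseline with final scores by a paired t-test or Wilcoxon test and does not set such scores apart.

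**Working it through.** The article gives no figure to reproduce here. The check is a reading of the text with some supporting arithmetic.

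**1. Who is covered.** The Background defines stillbirth as death in the womb from 20 weeks up to the moment before birth. A woman with a repeat stillbirth therefore still gives birth. If this happens before she completes the protocol, she meets the wording of the contact rule. A late termination for medical reasons falls under the same literal reading, and the eligibility criteria group it with stillbirth. A loss before 20 weeks is not clearly a birth, and the article states no contact rule for it.

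**2. What she would be invited to complete.** The rule refers to the post-intervention questionnaires without listing them. The worry score is marked at that time point in Table 2. The tick marks in the self-management row cannot be assigned safely to its two instruments, so inclusion of the prenatal coping inventory rests on the general statement in the Method section that outcome measures are completed before and after the intervention.

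**3. Internal consistency.**
- The discontinuation criteria separate no longer being pregnant from delivering. The contact rule uses one term, giving birth, for everyone.
- The Data collection section says that collection stops at birth, and in the next sentence that final data will be sought.

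**4. How easily the rule is triggered.** Entry is allowed below 30 weeks, and the treatment window is 4 months.
- Window in weeks: 4 × 365.25 / 12 / 7 = 17.4.
- Latest entry, 29 weeks and 6 days: 29.86 + 17.39 = 47.25 weeks at the end of the window.
- Taking 40 weeks as a reference point: 40 − 17.39 = 22.6. Any entry after about 22.6 weeks has a window that runs past 40 weeks.
- Taking 37 weeks: 37 − 17.39 = 19.6.

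Birth before completion is therefore foreseeable for many participants unless they take their massages early.

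**5. Chance of at least one loss.** The article gives no risk of repeat loss, so the risk p per woman is an assumption. With n = 75 (Sample size section), the expected number is 75p and the chance of at least one is 1 − (1 − p)^75.

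| Assumed p | Expected losses | Chance of at least one |
|---|---|---|
| 0.5% | 0.375 | 31% |
| 1% | 0.75 | 53% |
| 2% | 1.5 | 78% |
| 3% | 2.25 | 90% |

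These figures count any further loss at any time. The rule reaches only losses that involve birth and occur before protocol completion, so for each p the figure is an upper bound.

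**6. Effect on the Q.M criterion.** On the same assumptions, 0.375 to 2.25 women out of 75 is 0.5 to 3 percentage points. The amber band runs from 60% to 80%, a width of 20 points.

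**The case against.** The strongest reply is that this is an article. A bereavement procedure may well sit in the full protocol, the ethics submission or the adverse-event file, none of which is shown. The section also reads as if written about running out of gestation: it presents the entry limit at 30 weeks as the safeguard against birth before completion. The separate wording in the discontinuation criteria suggests that the authors think of loss as its own category. And the e-mail is only an invitation to women whose participation is voluntary.

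Much of this stands as a limit on the point. A reader might infer that the trial has no bereavement procedure; the article cannot show that. A reader might infer that every woman who gives birth is e-mailed under this rule; it covers only birth before completion. A reader might infer that, if the rule means live births only, bereaved women get no end-of-study contact; on that reading the article is merely silent. The timing of the first e-mail is not given either, so how soon after a loss it would arrive is unknown.

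A reader might also infer that Q.M answers from bereaved women would distort progression. The documents do not support this: the possible effect is small, the denominator is not defined, and that such an answer would reflect the loss rather than the massage is conjecture.

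The reply does not dispose of the rule itself. The article did not leave contact to another document. It states the recipients, the content and the timing of the follow-up, without a condition or a cross-reference. The therapists' grief training and adverse-event reporting, both mentioned elsewhere, do not restrict the e-mails.

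**Conclusion.** The point holds as a stated rule that is badly fixed, not as a missing procedure. As printed, the invitation and the follow-up reach any woman who gives birth before completion, including after a repeat stillbirth, and the terms do not match the discontinuation criteria. For any one woman the event is unlikely. Across 75 women the chance of at least one loss is at most 31% to 90%, resting wholly on assumed risks of 0.5% to 3%.

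The main stake is avoidable distress to a woman affected. The statistical stake is wider: pregnancy-specific scores obtained after any birth, including a live one, are not comparable with baseline, and the window length makes such scores foreseeable. A correction confined to bereaved women would therefore be incomplete. The correction is worth making because it costs so little.

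**What to change.** Amend the Data collection section as follows.

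- Confirm the outcome of the pregnancy before any post-birth invitation or follow-up is released.
- After a loss, replace the standard e-mail and automatic follow-up with an optional, separately worded contact that omits the pregnancy-specific scales.
- Report women with a further loss separately in the participant flow and in the Q.M progression criterion.
- Keep pregnancy-worry and prenatal-coping scores completed after any birth out of the main paired comparison, or report them separately.
- Reconcile the terms used in the Data collection section with those in the discontinuation criteria, and reconcile the statement that data collection stops with the plan to seek final data. If an unseen file already holds a procedure for loss, refer to it here.

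The cost is a short amendment, which by the article's own terms needs ethical approval, and a status check before each message. A few end-of-study questionnaires will be missing or reported apart, and the paired comparison of the two pregnancy-specific scales will rest on fewer women. No treatment rule changes.

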## Data analysis

### Analysis of quantitative data

The participant’s demographic and clinical characteristics will be summarised using descriptive statistics. Summary statistics of the observational clinical treatment data (e.g. worry, anxiety, etc.) will be reported and an appropriate matched test will be used to determine significant differences between baseline and post-final treatment scores (e.g. paired *t*-test if data are normally distributed, Wilcoxon matched-pairs test if not).

Three treatment effect modifiers have been identified: (1) the amount of other support services utilised, (2) passing the gestational age during the study intervention that they experienced their stillbirth, (3) the time between the stillbirth and this pregnancy, and (4) the number of study intervention treatments received. The correlational analysis will be used to determine associations between observational treatment outcomes and support services utilized (e.g. talk therapy (psychology/counselling), peer support etc.). Appropriate comparative tests will be used to determine whether there is a relationship between observed treatment outcomes and gestation of stillbirth, the duration of the interpregnancy interval, and the number of treatments administered.

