### Study design

The study is a convergent parallel mixed-methods, single-arm repeated measures pilot trial design.

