
Researchers in the iCHOOSE Study are developing a core outcome set for stillbirth care research (55, 56), and this will guide future outcome measures for stillbirth research. The validated self-reported questionnaires evaluating worry and anxiety have been used together in previous research as outcome measures in stillbirth research (57) and influenced our use of these outcome measures. Worry, anxiety and stress have ‘intertwined behavioural and neural underpinnings’ (58); however, they have important unique characteristics that impact the way that they are experienced. Evaluating worry, stress and anxiety allows the researchers to capture the potential varied psychological states that can occur throughout a pregnancy after stillbirth especially when milestone events are passed without bad news/harm (e.g. gestation of previous loss, genetic and or anomaly scans).

*A post-intervention qualitative questionnaire* designed by the study researchers was based on a questionnaire used in previous stillbirth and massage research (36) (see Additional file 4) and assesses treatment utilisation and acceptability (Q.A-D), the appropriateness and suitability of the validated outcome measures the study used (Q.E), participant’s views of the study benefits (Q.G-L) and the participants’ perception of the study intervention to be a support for pregnant individuals via a massage intervention (Q.M).

An *in-depth interview* is intended to collect rich descriptions of participant experiences of massage and identify important aspects of care as well as provide information on the acceptability of the study intervention. Twenty study participants will be interviewed using a semi-structured approach by the study PI. The interviews will be conducted online via Zoom, recorded and transcribed verbatim by Cockatoo AI transcription services (59).

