#### Progression criteria: Intervention implementation and experience

Assess the feasibility of delivering and experiencing the intervention in a way that is acceptable to pregnant women who have previously experienced stillbirth/TFMR.Red: Delivery and experience of intervention judged possibly feasible by qualitative data.Amber: Delivery and experience of intervention judged feasible by qualitative data.Green: Delivery and experience of intervention judged strongly feasible by qualitative data.

The methodology and design of the HOPES study use a model of integrating the participant as the expert on their needs for support and care during pregnancy after a stillbirth and reflects elements considered essential by families who have experienced a subsequent pregnancy after stillbirth. Specifically, Gower et al. found a high-quality excellent care involved affirming and recognising pregnant people’s anxiety while being kind and empathetic and incorporating individualized emotionally supportive care (4). This is reflected in the study design via the conceptual approach that massage is just more than the hands-on application of treatment and via the participants being able to make therapeutic decisions about what they require addressing at each treatment session as well as determining the timing of their treatments to meet their unique needs. A participant-centred, participant-led approach in clinical practice has been shown to improve satisfaction with the care experience and improve health outcomes (70, 71).

A key study strength is the application of the intervention in a real-world setting. This allows the researchers to analyse the potential effects and benefits of massage in a setting relatable to how massage is currently provided. This is important in translating any findings into practice and allowing commercial massage therapists to incorporate this type of massage into their practice. The sample selection bias due to participants self-selecting to participate in the study is a study limitation, but this sample is reflective of the clinical practice where consumers self-select to seek massage treatment. The lack of a comparison group may be considered a limitation of this study; however, the challenges of deploying an individual randomised-controlled trial design are recognised among researchers active in care in pregnancy after loss (15).

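### The named modifier is passing the gestation of the earlier loss during the study, but the analysis sentence tests the gestation of that loss, which is a different variable

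*Protocol article*

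**What the plan says.** The section on analysis of quantitative data opens its modifier paragraph with "Three treatment effect modifiers have been identified" and then numbers four: use of other support services, "passing the gestational age during the study intervention that they experienced their stillbirth", the time from the stillbirth to this pregnancy, and the number of study treatments received.

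Two analysis sentences follow. Correlation is planned for support services. Comparative tests are planned for the remaining variables, and the question put to them reads: "whether there is a relationship between observed treatment outcomes and gestation of stillbirth, the duration of the interpregnancy interval, and the number of treatments administered".

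The outcome in question is within-person change: "an appropriate matched test will be used to determine significant differences between baseline and post-final treatment scores". The design is a "single-arm repeated measures pilot trial design". The section on the self-reported questionnaires justifies measuring worry, stress and anxiety together because psychological states vary through the pregnancy, "especially when milestone events are passed without bad news/harm (e.g. gestation of previous loss, genetic and or anomaly scans".

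**The concern.** The second modifier needs three pieces of information: gestation at the earlier loss, gestation at baseline and gestation at the post-measure. The variable in the analysis sentence uses only the first. If the analysis is run as written, the report will say whether women with earlier or later losses changed differently. It will not say whether women who got past the feared point between their two measurements changed differently.

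The second question is the one the plan set itself, and the article gives it substance by naming the gestation of the previous loss among the events around which psychological states vary. A pre/post change in anxiety could partly reflect having passed that point. The analysis that could show this is not the one described.

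A lesser matter is the label. Calling these variables treatment effect modifiers implies that a massage effect can be isolated and compared between subgroups. With one arm, only the association of each variable with change can be estimated.

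**Working it through.** The plan gives no figure for this point, so there is none to reproduce. The check compares the two definitions and then asks whether one could stand in for the other.

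**Step 1. Match the list to the analyses.**

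| Modifier as listed | Variable in the analysis sentences | Same variable? |
|---|---|---|
| Other support services used | Support services used | Yes |
| Passing the gestation of the loss during the study | Gestation of the stillbirth | No |
| Time from stillbirth to this pregnancy | Interpregnancy interval | Yes, reworded |
| Number of study treatments | Number of treatments | Yes |

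**Step 2. Classify women under the protocol's own limits.** Table 1 sets entry gestation e below 30 weeks and loss gestation L from 20 weeks. The intervention section sets a 4-month window, which is 4 × (365.25/12)/7 = 17.4 weeks. With the full window used, the milestone is:
- passed before baseline if L ≤ e;
- passed during the study if e < L ≤ e + 17.4;
- not reached if L > e + 17.4.

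For a loss at 28 weeks:
- entry at 10 weeks gives 10 + 17.4 = 27.4, so not reached;
- entry at 22 weeks gives 39.4, so passed during the study;
- entry at 29 weeks means it was passed before baseline.

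One value of the analysed variable covers all three states. This step needs no assumption about how entry gestations are distributed.

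**Step 3. Size, under an assumed distribution.** The article does not give the distribution of entry gestation. Assume it is uniform over 12 to 30 weeks, with the full window used and birth ignored. Then

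P(pass during) = [min(30, L) − max(12, L − 17.4)] / 18.

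| Loss gestation (weeks) | Calculation | Pass during | Remainder |
|---|---|---|---|
| 20 | (20 − 12)/18 | 44% | 56% before |
| 24 | (24 − 12)/18 | 67% | 33% before |
| 29.4 | (29.4 − 12)/18 | 97% | 3% before |
| 36 | (30 − 18.6)/18 | 63% | 37% not reached |
| 40 | (30 − 22.6)/18 | 41% | 59% not reached |

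The share rises and then falls, so a monotone test on loss gestation is not even a rough proxy for the milestone.

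**Step 4. Vary the assumption.** In a simulation, loss gestation was uniform over 20 to 40 weeks and entry uniform from 8, 12 or 16 up to 30 weeks, with a 17.3-week window cut off at 40 weeks. Overall, 64%, 70% or 74% pass during the study. The correlation between loss gestation and passing is −0.18, −0.03 or +0.23. It is weak, and its sign depends on when women enrol.

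**Step 5. What a single arm can show.** Suppose massage has no effect and passing the milestone alone shifts the change score by δ standard deviations (assumed). Take the article's minimum sample of 50, split 25/25. The standard error is √(1/25 + 1/25) = 0.283, and

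P(significant) = Φ(δ/0.283 − 1.96) + Φ(−δ/0.283 − 1.96).

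For δ = 0.3, 0.5 and 0.8 this is 0.185, 0.42 and 0.81. A clear association with the milestone can therefore appear with no massage effect to modify.

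**The case against.** The best defence is that the analysis sentence uses shorthand. The second variable sits in the expected place in the list, another item is reworded between list and analysis, and comparative tests would suit passed versus not passed. A condensed article may leave variable derivation to a fuller document. This reading is possible, and a reader should not conclude that the investigators certainly intend the wrong test. But the third item is reworded to a synonym, whereas the second is reworded to a different quantity. The published sentence still directs a different analysis, and adjacent sentences need reconciling.

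On the single-arm point, much of the defence stands. The analysis sentences speak only of associations and a relationship, which one arm can estimate, and the discussion concedes that "The lack of a comparison group may be considered a limitation of this study". The fault lies in the modifier label and in any interpretation built on it. The tests themselves are not invalid.

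Three further inferences are tempting but unsupported:
- That the milestone is the main rival explanation for change. The article gives it as one example beside genetic and anomaly scans and does not rank it.
- That distress drives the number of massages. The article ties number and timing to participant preference, therapist planning, obstetric advice and birth.
- That loss gestation misplaces a fixed fraction of women, such as a third. That figure follows from picking 24 and 36 weeks. Under the same assumptions the minority share runs from about 3% to 44%.

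**Conclusion.** The concern holds. The variable in the analysis sentence is not the second modifier, and under the protocol's entry, loss and window limits it cannot substitute for it. That conclusion rests on the documents alone. The range of about 41% to 97% passing during the study rests on the assumed uniform entry over 12 to 30 weeks and full use of the window. Massages are up to five at chosen intervals and birth ends treatment, so actual follow-up will often be shorter and the shares will differ.

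The consequence is limited. Feasibility and acceptability are the primary outcomes, and none of the progression criteria uses these analyses. What is at stake is whether the secondary results answer the question the plan poses, and whether they are described in terms the design supports. Listing four items under the word three is a plain slip.

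**What to change.** 1. In the analysis sentence, replace the gestation of the stillbirth with a variable derived from gestation at loss, at baseline and at the post-measure: passed before baseline; passed between baseline and post-measure; not reached while still pregnant.
2. Identify separately the women who gave birth before the post-measure. The data collection section allows them to answer afterwards, and they should not be pooled with women for whom the milestone still lies ahead.
3. Relate this variable to the post score adjusted for baseline, or to the change score. Either is acceptable. Gestation of loss may stay as a separate descriptive covariate.
4. Describe all four variables as exploratory associations with change. Treat the number of massages as a post-baseline exposure that birth or obstetric advice can cut short.
5. Correct the count to four.

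The cost is some extra derivation and analysis. Gestation at loss is needed for eligibility and for the purposive sampling, gestation at entry is screened, and massage dates are recorded under Table 2. No new questionnaire is needed, provided the dates of the post-measure and of any birth are kept.
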